### Power analysis and statistical analysis

Power estimates were calculated using the G* Power 3 programme [103]. Treatment effects will be investigated by an intention-to-treat approach to data analysis using a hierarchical linear model, whereby therapists will be included at the second level to account for potential nesting by this factor. Power analysis for effects are estimated with conservative repeated measures analysis of variance (ANOVA) (within-between interactions). For the primary outcome measure, based on previous studies [22, 28], the difference in effect size is set to *d* = 0.35, alpha = 0.05, correlation between repeated measures 0.5, two measurements (pre/post), a total of 70 subjects (*n* = 35 in each group) yielding power above 0.82. Moderators and mediators will be investigated using linear multiple regression, fixed model, single coefficients. An effect size set to *f*^*2*^ = 0.15, two-tailed tests, alpha = 0.05 and *N* = 70 yields power above 0.95 with four predictors. For the subset of functional MRI (fMRI) assessments the following statistics and power analysis will be applied: task-fMRI data will be analysed using General Linear Model in SPM12 for pre-processing and single subject and group analyses, GIFT [104] to investigate the functional and structural data, and arterial spin labelling (ASL) data will be analysed in SPM12. Region of interest (ROI) will be analysed for both structural and functional data (SPM12) to extract blood oxygen level dependent (BOLD) responses to test correlation with specified variables. Expecting percent signal changes of approximately 0.5% at the single voxel and spatial smoothing at full width at half maximum (FWHM) of 5 mm (provides an estimated effect size of *d* = 0,7), using the two-tailed independent samples *t* test, an allocation rate of 1, alpha set to 0.05, correlation between repeated measures 0.5 and a total sample size of 80 (40 in each group) yields power above 0.87. For differences between pre-treatment and post treatment data using the same parameters, the matched-pairs *t* test with 20 subjects yields power above 0.90. Treatment effects are estimated using conservative repeated measures ANOVA (within-between interaction), and conservatively setting the estimated value of *d* = 0.35, alpha set to 0.05, two measurements (pre, post), correlation between repeated measures 0.5, and 60 subjects (*n* = 20 per group) yields power above 0.83. Based on these calculations, the estimated power values indicate that risk of committing type II errors is adequately controlled.

To control for type 1 errors, the secondary clinical outcome inventories will be assessed in two stages, initially together, and if significant they will be analysed separately. Pre-treatment differences on continuous and categorical demographic variables between the two treatments will be assessed using the independent samples *t* test and Fisher’s exact test, respectively. Other changes and differences in continuous variables will be assessed using the repeated and independent samples *t* test, and Fisher’s exact test and McNemar’s test to determine proportional differences between or within groups, respectively. Repeated testing within the same domain will be controlled for multiple testing using the Holm-Bonferroni method [105].

Missing data will be handled within the hierarchical linear model analyses. For analyses where this is not appropriate, last observation carried forward (LOCF) will be applied. For inventories, missing data will be replaced by the mean, provided that no more than 20% of values/item for this measure are missing. If more than 20% of values/item are missing, data will be considered invalid, and will be handled as missing as described. The potential impact of compliance with the different treatment elements will be addressed in separate analyses.

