**Methods:**

The sample comprises 70 participants aged 60–75 years, who have GAD. Exclusion criteria comprise substance abuse and unstable medication; inability to participate in physical exercise; and conditions which precludes GAD as primary diagnosis. The interventions are individual treatment in the outpatient clinic at the local psychiatric hospital, with two experimental arms: (1) CBT + physical exercise and (2) CBT + telephone calls. The primary outcome measure is symptom reduction on the Penn State Worry Questionnaire. Other measures include questionnaires, clinical interviews, physiological, biological and neuropsychological tests. A subset of 40 participants will undergo magnetic resonance imaging (MRI). After inclusion, participants undergo baseline testing, and are subsequently randomized to a treatment condition. Participants attend five sessions of the add-on treatment in the pre-treatment phase, and move on to interim testing. After interim testing, participants attend 10 sessions of CBT in parallel with continued add-on treatment. Participants are tested post-intervention within 2 weeks of completing treatment, with follow-up testing 6 and 12 months later.

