## Method

### Study design

The study is a 2 × 2 mixed factorial design (Time x Group) with participants randomized to one of two treatment conditions: (1) CBT combined with physical exercise (CBT + PE) or (2) CBT combined with telephone call attention placebo (CBT + AP). Participants complete pre-treatment, interim and post-treatment outcome measures, in addition to follow-up tests at 6 and 12 months after treatment.

Participants in both treatment conditions attend a 5-week pre-treatment period. The pre-treatment period has a two-part rationale. The first 5 weeks of physical exercise are aimed at introducing the participant to the exercises with a focus on adjustment and neuromuscular facilitation [64]. In addition, resting BDNF has been shown to increase after 5 weeks of physical exercise [65]. The primary goal of the pre-treatment period is to ensure good implementation of physical exercise, and to obtain elevated resting BDNF in the CBT + PE group before the onset of CBT. As such, the pre-treatment period is a measure to facilitate the add-on effects of physical exercise.

Participants receiving CBT + PE attend one supervised and two unsupervised sessions of PE during each of the 5 weeks of the pre-treatment period. Participants receiving CBT + AP receive one telephone call per week during the pre-treatment period.

After the pre-treatment period, the participants receive 10 weekly sessions of CBT combined with either continued physical exercise in the participants receiving CBT + PE or weekly telephone contact in parallel to the CBT sessions in the participants receiving CBT + AP. See Fig. 1 for a display of the study design. The present protocol has been prepared in accordance with relevant items from the Standard Protocol Items: Recommentations for Interventional Trials (SPIRIT) Checklist (see Additional file 1). See Fig. 2 for the SPIRIT figure displaying the schedule of enrolment, interventions and assessments.

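### The PSWQ treatment effect is framed as an unadjusted Time x Group change contrast, which at the protocol's own correlation of 0.5 has about 25% less precision than a baseline-adjusted one

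*Protocol article*

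**What the plan says.** Four statements in the Protocol article bear on the form of the treatment effect.

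- **Outcome** (Abstract, Methods): "The primary outcome measure is symptom reduction on the Penn State Worry Questionnaire".
- **Design** (Study design): "The study is a 2 × 2 mixed factorial design (Time x Group) with participants randomized to one of two treatment conditions".
- **Power** (Power analysis and statistical analysis): "Power analysis for effects are estimated with conservative repeated measures analysis of variance (ANOVA) (within-between interactions"; for the primary outcome, "the difference in effect size is set to *d* = 0.35", with "alpha = 0.05, correlation between repeated measures 0.5, two measurements (pre/post), a total of 70 subjects", 35 per arm, and a stated power above 0.82.
- **Other continuous variables** (same section): "Other changes and differences in continuous variables will be assessed using the repeated and independent samples" t tests.

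The primary model gets one sentence. It is an intention-to-treat analysis "using a hierarchical linear model, whereby therapists will be included at the second level to account for potential nesting by this factor". No fixed effects are listed, and therapist is the only higher-level unit named. The same section says that missing data will be handled within this model. The only stated use of pre-treatment differences is to test demographic variables between arms.

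**The concern.** Read together, the outcome, the design and the power calculation describe the effect as the difference between arms in mean pre-to-post change. With complete pre/post data and a separate baseline mean for each arm, that is exactly what a Time x Group term estimates. Randomisation follows baseline testing, so both arms have the same expected baseline PSWQ, and an unadjusted change contrast makes no use of that.

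Subtracting the whole baseline score over-corrects whenever the pre/post correlation is below 1. The baseline noise that this adds costs precision on the primary outcome. In a trial of 70, information that is already collected and costs nothing is worth using. Conditioning on baseline also removes the effect of chance baseline imbalance, which can be noticeable at 35 per arm.

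A separate question concerns the hierarchy. With five test points per participant, a model that has therapist as its only higher level could be read as having no participant level.

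**Working it through.** **Inputs.** From the section on power and statistical analysis: d = 0.35, alpha = 0.05, rho = 0.5, two measurements, N = 70, 35 per arm. SD is taken as equal at both times and in both arms, which is an assumption.

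**1. Reproduce the stated power.** For the within-between interaction, take f = d/2 = 0.175.

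lambda = f² × N × m / (1 − rho) = 0.030625 × 70 × 2 / 0.5 = 8.575.

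Noncentral F on 1 and 68 df gives power 0.823, which matches the stated figure.

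**2. Effect implied by that power.** The change score has variance 2(1 − rho) = 1.00 SD². Setting delta² × 35 / (2 × 1.00) = 8.575 gives delta² = 0.49, so delta = 0.70 SD difference in change.

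**3. Compare the two contrasts** (per-participant variance, large sample).

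- Change: 2(1 − rho) = 2 × 0.5 = 1.00 SD².
- Baseline-adjusted: 1 − rho² = 1 − 0.25 = 0.75 SD².
- Ratio: (1 + rho)/2 = 0.75. The share of precision lost is (1 − rho)/2 = 25%, and the standard error ratio is √0.75 = 0.866.
- Equivalent sample size: 70 / 0.75 = 93.

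**4. Sensitivity to rho.** The article gives no other value, so this range is an assumption.

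| rho | change | adjusted | precision lost | power at 0.70 SD, change | power at 0.70 SD, adjusted |
|---|---|---|---|---|---|
| 0.3 | 1.40 | 0.91 | 35% | 0.684 | 0.857 |
| 0.5 | 1.00 | 0.75 | 25% | 0.823 | 0.915 |
| 0.7 | 0.60 | 0.51 | 15% | 0.961 | 0.981 |
| 0.8 | 0.40 | 0.36 | 10% | 0.995 | 0.998 |

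Powers use the noncentral t with 35 per arm (68 df for change, 67 df adjusted). For 82% power at rho 0.5 and 0.70 SD, the normal approximation needs 34 per arm unadjusted and 26 adjusted. If d = 0.35 is instead read directly as the between-arm difference in change, power goes from 0.303 to 0.385.

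**5. Small-sample check.** In 20,000 simulated trials at rho 0.5 and 35 per arm, the adjusted estimate had variance 0.0436 and the change estimate 0.0570. The ratio is 0.765, a loss of 23.5%. Estimating the slope takes back a little of the gain.

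**6. The participant level, taken separately.** Suppose pre and post scores are fitted as separate occasions with no participant effect, and there is no therapist variance. The model then treats four cell means as independent.

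- Model SE: √(4/35) = 0.338 SD (simulated mean 0.337).
- True SE of the change contrast at rho 0.5: √(2 × 1.00/35) = 0.239 SD (simulated 0.239).
- Ratio: √2, or 1.41. Simulated type I error was about 0.006, and power at 0.70 SD was 0.55 instead of 0.82.

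This figure is conditional on that model being fitted. It is no part of the 25%.

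**The case against.** The strongest reply is that the hierarchical model is described in one sentence of a journal article. Covariates and covariance structure are commonly left to an analysis plan, so silence does not show that baseline PSWQ is left out. The power model is a simplification labelled conservative and need not define the estimator. A model with a Time x Group term can also constrain baseline means to be equal and so recover most of the gain. Much of this stands: the article does not rule out adjustment, and nobody can say from it that the final model will lack it. What remains is that every statement the article does make (outcome, design, power, t tests) points to unadjusted change, and none points the other way.

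It is also fair that the t tests include within-group changes, for which a baseline-adjusted arm contrast is not the relevant analysis. The secondary clinical inventories have their own two-stage procedure. The recommendation on t tests is therefore limited to between-arm comparisons.

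A reader might infer three stronger things that the documents do not support.

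- **That at least a quarter of precision is lost.** A quarter is the large-sample value at rho 0.5, not a floor. The loss is smaller at any higher correlation.
- **That naming only therapists at level two makes the standard error wrong.** Participants at level one nested in therapists is a coherent reading. The √2 inflation arises only if occasions are level one and no participant effect is fitted, which the article does not say.
- **That the stated power fails for this reason.** The figure was computed on the unadjusted contrast and reproduces. Adjustment improves on it and does not repair it. How d was entered is a different question.

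**Conclusion.** The point holds as a matter of efficiency. The unadjusted difference in change is unbiased under randomisation and matches the stated outcome of symptom reduction, but it leaves available precision unused. At the protocol's own rho of 0.5 the loss is about 25% in large samples and about 23.5% at 35 per arm; in general it is (1 − rho)/2. At the 0.70 SD effect implied by the stated power, adjustment moves power from about 0.82 to about 0.92.

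These sizes assume equal SDs before and after treatment, a linear relation between the two scores, complete pre/post data and no therapist variance. They also take the contrast as the article frames it; if the full plan already conditions on baseline, only the wording of the article needs attention.

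The missing mention of a participant level is a separate clarification. It would be serious only if the level were in fact omitted, and the text does not establish that.

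**What to change.** In the section on power and statistical analysis:

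1. State that the primary estimate is the arm difference in PSWQ at post-treatment from the hierarchical model, either with baseline PSWQ as a covariate or with a common baseline mean constrained across arms.
2. Use the same baseline-adjusted form for between-arm comparisons of the continuous outcomes now assigned to t tests. Within-group tests of change are not affected.
3. As a separate sentence, if repeated occasions are modelled, say that occasions are nested in participants and participants in therapists.

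The cost is analysis wording only. Baseline questionnaires are completed before randomisation, so no new data, visits or participants are needed. The choice should be fixed before outcome data are compared by arm, so that adjustment cannot be selected on the result.

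### The primary power of 0.82 belongs to a 0.70 SD between-arm difference in change; at the stated d = 0.35, 35 per arm gives about 0.30

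*Protocol article*

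**What the plan says.** All of this is in the Protocol article, Power analysis and statistical analysis. On the tool, it says "Power estimates were calculated using the G* Power 3 programme". On the test, it says "Power analysis for effects are estimated with conservative repeated measures analysis of variance (ANOVA) (within-between interactions". For the primary outcome, "the difference in effect size is set to *d* = 0.35, alpha = 0.05"; the remaining inputs are "correlation between repeated measures 0.5, two measurements (pre/post" and 70 participants in total. The result is "35 in each group) yielding power above 0.82".

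After the regression and imaging calculations, the section concludes that "the estimated power values indicate that risk of committing type II errors is adequately controlled". It gives neither the f value entered nor the conversion from d to f.

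The comparison that this power has to serve is stated at the end of the Background and again in the Discussion: a larger PSWQ reduction with CBT plus exercise than with CBT plus telephone calls. That is a between-arm difference in pre-to-post change.

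**The concern.** A two-arm trial with 35 per arm has little power for a standardised difference of about a third of an SD, unless the repeated measures are very highly correlated. The plan puts the correlation at 0.5. With two measurements, that gives a change score the same SD as a single measurement, so the change score brings no gain in precision. A power above 0.82 therefore looked far too high for an effect of 0.35.

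This is the only power statement for the primary outcome. If it is wrong, the trial is presented as adequately powered for an effect that it would usually miss. A non-significant PSWQ result could then be read as evidence against exercise augmentation when the trial could not have settled the question.

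**Working it through.** **Inputs, all from the power section:** d = 0.35; alpha = 0.05; ρ = 0.5; m = 2 measurements; N = 70, 35 per arm; within-between interaction. The interaction F test has 1 and 68 degrees of freedom and is equivalent to a two-sided t test on change scores.

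**Step 1. Reproduce the stated figure.** For this test G*Power uses λ = f²·N·m/(1 − ρ), which here is f² × 70 × 2/0.5 = 280·f².

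| f entered | λ | Power |
|---|---|---|
| 0.35 (d itself) | 34.3 | above 0.999 |
| 0.175 (d/2) | 8.575 | 0.823 |
| 0.0875 (d/4) | 2.144 | 0.303 |

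Of these, only f = 0.175 matches the article.

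**Step 2. What f = 0.175 means in this design.** The rule f = d/2 applies to the main effect of two group means, where each mean lies d/2 from the grand mean. In a 2 × 2 interaction, a between-arm difference in change of Δ is spread over four cells, each with an interaction effect of ±Δ/4. Hence f = Δ/(4·SD).

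- f = 0.175 gives Δ = 4 × 0.175 = 0.70 SD.
- Δ = 0.35 SD gives f = 0.35/4 = 0.0875.

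**Step 3. Check without any f.** The SD of change is SD × √(2(1 − 0.5)) = SD. The interaction test is then a two-sample t test on change with n = 35 per arm and noncentrality d·√(n/2) = d × √17.5 = 4.183·d.

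- d = 0.35: noncentrality 1.464 (squared, 2.144), power 0.303.
- d = 0.70: noncentrality 2.928 (squared, 8.575), power 0.823.

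These agree with Step 1. Simulation of 40,000 trials gives 0.305 and 0.823.

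**Step 4. What 35 per arm can detect.** The detectable difference is 0.68 SD at 80% power. Power of 0.82 at 0.35 SD needs 136 per arm (t distribution; 135 by normal approximation).

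**Step 5. Could another reading reach 0.82 at 0.35 SD?**

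| Variant at 0.35 SD, 35 per arm | Power |
|---|---|
| One-sided test, ρ = 0.5 | 0.42 |
| Baseline-adjusted analysis, ρ = 0.5 | 0.38 |
| Change score, ρ = 0.3 | 0.23 |
| Change score, ρ = 0.7 | 0.46 |

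Reaching 0.82 by correlation alone needs ρ of about 0.87. Standardising by the SD of change in place of the raw SD alters nothing, because the two are equal at ρ = 0.5.

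**The case against.** **The conversion is inferred.** The article states no f. The same section's other d = 0.35 interaction calculation (60 participants, power above 0.83) does not come out with f = 0.175, which gives 0.65 with three groups or 0.76 with two. A single-group pre/post t test of 0.35 SD in all 70 participants also gives 0.823 (noncentrality 0.35 × √70 = 2.928), so the route to 0.82 is not certain. This stands as a caution about how the figure arose. It does not affect the 0.303, which follows from the stated inputs alone.

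**The intended effect may have been 0.70 SD.** If 0.35 were each arm's deviation from the average change, the gap between arms would be 2 × 0.35 = 0.70 SD and the power would be right. The studies cited for the effect size cannot be consulted here. But the article words the quantity as a difference between effects ("the difference in effect size is set to" d = 0.35), which does not fit that reading. The fix allows for either intention.

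**The planned analysis is a hierarchical linear model, and the ANOVA is called conservative.** The model's power may differ, so the 7-in-10 miss rate belongs to the pre/post ANOVA calculation. The article rests its claim on that ANOVA, however, and baseline adjustment at ρ = 0.5 raises power only to 0.38.

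**Dropout and therapist clustering.** The calculation mentions neither. An article may leave an attrition allowance to the full protocol, and the effect of clustering cannot be quantified from what is given. These are side remarks. As an illustration, an assumed 15% loss leaves about 60 participants (70 × 0.85 = 59.5); then λ = 0.175² × 60 × 2/0.5 = 7.35, and power is 0.76 even at 0.70 SD.

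**The type II sentence covers every calculation in the section.** This is fair: the present point undermines it for the primary outcome only.

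**Conclusion.** The concern holds. At the article's own inputs, power for a between-arm difference in change of 0.35 SD is 0.303, not above 0.82. The stated power is correct only for a difference of about 0.70 SD, twice the stated effect. The implied type II error at d = 0.35 is 1 − 0.303 = 0.697, so the assurance that it is adequately controlled is wrong for the primary outcome.

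This rests on the stated correlation of 0.5, two-sided alpha of 0.05 (implied by the F test), 35 analysed per arm, and d read as the difference between arms. Varying the correlation from 0.3 to 0.7 moves the power only from 0.23 to 0.46. The error must be corrected, because it is in the power statement for the primary outcome.

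**What to change.** Restate the primary power in one of two ways, according to which effect was intended:

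- 70 participants give power of about 0.30 for a between-arm difference in change of 0.35 SD; or
- 70 participants give power of 0.82 only for a difference of about 0.70 SD (80% for 0.68 SD), with a justification for expecting an effect of that size.

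In either case give the f value entered and define it as Δ/(4·SD). Withdraw the statement on type II error for the primary outcome. Say that a non-significant PSWQ result will be interpreted from its confidence interval and not as absence of effect.

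If the primary model adjusts for baseline PSWQ, the corresponding figures at ρ = 0.5 are power of about 0.38 for 0.35 SD and a detectable difference of about 0.59 SD (0.68 × √0.75). This helps at no cost in participants but does not restore 0.82.

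The cost is wording and a less favourable stated power. No extra participants are needed, and neither allocation nor the planned test changes.

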Previous studies investigating long-term physical exercise as an adjunct to with CBT for treatment of anxiety disorders have shown mixed results. One study had null findings [57], two studies indicate benefits of adjunct physical exercise [58, 59] and one feasibility study concluded that add-on physical exercise is feasible and potentially beneficial [60]. The study that did not find positive effects of CBT combined with physical exercise was in a non-clinical sample [57], which suggest a limited added effect of physical exercise in a non-clinical population. A recent study on physical exercise combined with exposure therapy for panic disorder demonstrated the lack of a significant effect of adjunct physical exercise. The authors point to ceiling effects as the reason for the lack of effect of the add-on treatment, as exposure therapy already has high treatment efficacy [61]. This is in line with a point made by other authors, that physical exercise could be a more potent intervention in groups in whom treatment with CBT has limited effects (e.g. [62]).

Based on this rationale, the aim of the present study is to compare the effects of physical-exercise-augmented CBT to standard CBT combined with a placebo control condition. We expect that exercise-augmented CBT will yield better results than standard CBT as measured by our primary outcome measure, symptom reduction on the Penn State Worry Questionnaire (PSWQ) [23]. The proportion of patients who achieve remission as assessed by an independent clinical assessor using the Anxiety Disorders Interview Schedule for DSM-IV (ADIS-IV) [63], will be assessed as a secondary outcome measure. We also expect levels of BDNF at baseline to be positively related to treatment outcome, and that the participants that receive augmented CBT will improve significantly in the cognitive measures and in levels of BDNF following treatment as compared to the CBT alone group. Furthermore, we expect HRV to improve with exercise-augmented CBT, and that these changes will correlate with clinical change, and changes in cognitive functions and BDNF levels.

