## Discussion

Older adults are a rapidly increasing group. GAD is frequent in this segment of the population, and older patients with GAD often do not receive adequate and effective help through the current healthcare systems, due to priorities favouring younger adults or because of the absence of proper healthcare programmes. Comorbid somatic and psychiatric illnesses are common in GAD, and create a socioeconomic burden [7]. Thus, it is also highly socioeconomically relevant to develop effective treatment for older adults. More importantly, effective treatment can lead to an increase in quality of life for the individual suffering from a psychiatric disorder, as well as improving comorbid somatic disorders. As far as we know, the knowledge on augmented treatment for older adults with GAD is scarce, although previous studies have yielded promising findings. As GAD is prevalent in older adults, and the impact of treatment for this disorder seems reduced with age, it is essential to develop more effective interventions for this growing segment of our population. To the best of our knowledge, no previous studies have investigated CBT augmented with physical exercise in older adults with GAD.

The aim of the present study is to compare the effects of CBT combined with either physical exercise or telephone call attention placebo. We expect that participants receiving CBT + PE will have greater symptom reduction assessed by the PSWQ than participants receiving CBT + AP. Further we expect physical exercise to be an efficient add-on treatment strategy for older adults with GAD because of the benefits of physical exercise on cognitive functions, mediated by changes in BDNF and HRV. We do not expect telephone calls to affect cognitive functions through these mediators, although adding telephone calls to CBT might provide a placebo effect. With the telephone calls, we try to control for the added human contact in the physical exercise condition. The added attention could increase the participants’ focus on the CBT, and as such enhance the treatment efficacy. However, we take great care not to focus on therapeutic content, and kindly ask the participant to discuss the therapy with their CBT therapist, if they bring up CBT-related themes or questions. We also instruct the physical exercise therapists to refer to the CBT therapists for CBT-related question and themes.

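### Mediators are assigned to single regression coefficients with no condition that exercise moved the marker, and the stated power above 0.95 is about 0.89 for one coefficient and at most about 0.77 for a two-path test at the plan's effect size

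*Protocol article*

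**What the plan says.** Under Power analysis and statistical analysis, the protocol article gives moderators and mediators one shared method: "Moderators and mediators will be investigated using linear multiple regression, fixed model, single coefficients". The power statement follows at once: "An effect size set to *f*^*2*^ = 0.15, two-tailed tests, alpha = 0.05", with N = 70, which "yields power above 0.95 with four predictors". The same paragraph closes by concluding that the risk of type II error is adequately controlled.

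The Discussion states the mechanism to be shown. Exercise is expected to help "because of the benefits of physical exercise on cognitive functions, mediated by changes in BDNF and HRV".

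The exercise-to-marker step appears separately as a hypothesis. The Background expects that participants given augmented CBT "will improve significantly in the cognitive measures and in levels of BDNF following treatment as compared to the CBT alone group". The Discussion expects the same direction for HRV and BDNF. The statistical section assigns other changes and differences in continuous variables to t tests.

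No sentence connects these arm comparisons to the mediator regression, and no indirect effect or joint test of two paths is named.

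**The concern.** A mediation claim needs two links: the intervention changes the marker (path a), and the marker relates to the outcome given arm (path b). The coefficient of the marker in a regression for PSWQ addresses path b only. It can be large when path a is zero, for instance when BDNF or HRV rises with clinical improvement in both arms alike.

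Mechanism is a main purpose of this trial. The five-week lead-in is meant to raise resting BDNF before CBT starts, the pattern of test points was designed partly to study mechanisms, and the Discussion lists the mediator work as a strength. If path b is reported without being tied to path a, a correlate of recovery could be published as the way exercise works.

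The power statement adds to this. It describes one coefficient, not an indirect effect, and it is too high even for one coefficient. A null mediation result would then be read against a sensitivity that the trial does not have.

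**Working it through.** **Inputs from the protocol article (Power analysis and statistical analysis).** f² = 0.15, two-tailed alpha = 0.05, N = 70, four predictors, 35 per arm. No effect of exercise on any marker is given, so the values of d for path a below are assumptions.

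**Step 1: the plan's own figure.** For one coefficient in a fixed-model multiple regression:
- df = N − p − 1 = 70 − 4 − 1 = 65
- noncentrality = √(f² × N) = √(0.15 × 70) = √10.5 = 3.24
- two-tailed critical t on 65 df = 1.997
- power from the noncentral t distribution = **0.891**

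The stated figure, above 0.95, does not reproduce. Variants tried:

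| Variant | Power |
|---|---|
| Two-tailed, 1 to 5 predictors | 0.891 to 0.892 |
| One-tailed, 4 predictors | 0.941 |
| Omnibus test of 4 predictors | 0.704 |
| Two-tailed, N = 88 | 0.949 |
| Two-tailed, N = 89 | 0.951 |

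None reaches 0.95 at N = 70. By contrast, the primary-outcome statement ("a total of 70 subjects (*n* = 35 in each group) yielding power above 0.82") does reproduce: f = d/2 = 0.175, two measurements and correlation 0.5 give 0.823.

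**Step 2: what one coefficient shows if exercise does not move the marker.** Simulated trials (20,000 per scenario, repeated with 40,000) had 35 per arm and four predictors (marker, arm and two covariates), with path b at f² = 0.15. The joint test requires both path coefficients to be significant at two-sided 0.05.

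With path a = 0 the true indirect effect is zero:
- marker coefficient significant: about 86% of trials
- joint test significant: about 4% of trials

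The 86% is simply the power of path b. It is a little below 0.891 because the simulated marker varies from trial to trial and shares information with the covariates.

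**Step 3: power of the joint test when path a is real.** For two equal arms f² = d²/4, so f² = 0.15 on path a corresponds to d = √(4 × 0.15) = 0.775.

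| Exercise effect on marker (assumed) | Path a power | Joint-test power |
|---|---|---|
| d = 0.775 (f² = 0.15) | 0.88 | 0.76 to 0.77 |
| d = 0.5 (f² = 0.0625) | 0.52 to 0.53 | 0.45 to 0.46 |
| d = 0.35 | 0.30 | 0.25 to 0.26 |

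The ranges cover repeated simulation runs. Multiplying noncentral t powers gives slightly higher values: 0.891 × 0.891 = 0.794 and 0.540 × 0.891 = 0.481. The simulated values are preferred. All figures use the full 70 participants, as the plan does; any loss to follow-up lowers them.

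**The case against.** The best defence is that the sentence belongs to a run of power statements and echoes a power programme's label for a test. It says coefficients in the plural, does not name the outcome of each regression, and sets no criterion for declaring mediation. Two regressions, one per path, would fit its wording, and the joint test used above is itself two single-coefficient tests. The combining step could sit in a full protocol or analysis plan that is not shown.

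Much of this stands. A reader might infer that the plan commits the trial to calling a marker a mediator on one significant coefficient. The text does not say that, so the 86% is not the error rate of a stated rule. It shows what an unlinked path-b result can look like. A reader might also infer that the exercise-to-marker check is absent. It is not: the arms are to be compared on BDNF, HRV and cognition, and an unmoved marker would show there.

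A third tempting reading is that moderators are mishandled too. That is not supported. An arm-by-moderator interaction is one coefficient in a multiple regression and a proper moderation test. The Background statement "We also expect levels of BDNF at baseline to be positively related to treatment outcome" is a prediction hypothesis and is not labelled moderation.

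The defence does not reach two things. The article states a method for mediators and attaches a power to it, yet nothing ties the marker comparison to the mediation claim. And the printed power is wrong on its printed inputs, which no unseen document can mend.

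**Conclusion.** The point holds for mediators, in two parts.

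- **Missing link.** The stated method covers one link of the hypothesised chain. The other link is tested elsewhere, but is not made a condition for a mediation claim. The consequence is a possibility, not a certainty: a marker that follows PSWQ but was not moved by exercise could be reported as a mediator.
- **Power.** The figure above 0.95 should be about 0.89 for a single coefficient; this rests only on the plan's inputs. For a two-path test, power is about 0.77 if both paths have f² = 0.15, and about 0.46 if exercise shifts the marker by d = 0.5. These last figures rest on assumed marker effects, one marker at a time and no dropout. The closing assurance about type II error is therefore not supported for mediation.

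The primary PSWQ comparison is unaffected, so this is a matter for the mechanism claims. It should be corrected before those analyses are run.

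**What to change.** 1. For each mediator, state two regressions: marker on arm plus baseline marker and baseline PSWQ; and PSWQ on marker, arm and the same baselines. Claim mediation only if the indirect effect is supported, either by a confidence interval for the product of the two paths that excludes zero or by both paths being significant. Choose one criterion in advance.
2. If the full sequence from exercise through BDNF or HRV to cognition to worry is to be claimed, say so and add the further link. The two-regression model covers one marker at a time.
3. Correct the stated power from above 0.95 to about 0.89 for a single coefficient.
4. State indirect-effect power separately with its assumptions: about 0.77 with f² = 0.15 on both paths, and about 0.46 with a marker shift of d = 0.5. These apply to the both-paths-significant criterion and should be recalculated if the confidence-interval criterion is chosen.

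The cost is a few sentences, a few lines of code and a less favourable power statement. No new data or visits are needed.
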